#### EXPERIMENTAL DESIGN

After screening, 60 men and women who meet the criteria for study inclusion will be randomly assigned into 4 groups, with each group containing 15 subjects (n=15). The treatment period will start at week 0 and continue for 40 weeks total.  **During** **weeks 0-4**, *groups 1 and 2* will receive an oral placebo and *groups 3 and 4* will receive pioglitazone orally every day. **During weeks 5-40**, *group 1* will continue the oral placebo and self-inject a SQ placebo and *group 2* will continue the oral placebo and self-inject rhGH. Also **during weeks 5-40**, *group 3* will continue pioglitazone and self-inject a SQ placebo and *group 4* will continue pioglitazone and self-inject rhGH.

*Group 1* (n=15): Oral placebo plus SQ placebo.

*Group 2* (n=15): Oral placebo plus rhGH.

*Group 3* (n=15): Pioglitazone plus SQ placebo.

*Group 4* (n=15): Pioglitazone plus rhGH.

Sample size was determined using data from Johannsson et. al, 1997 in which a dose of rhGH comparable to ours was used to achieve a 17.9 +/- 3.5 percent change in visceral fat volume and an increase in insulin sensitivity of 1.2 +/- 0.6 mg/dl  hr over time (24). Using this information, we have powered our study based on 2 primary efficacy endpoints as follows: (a) 12 subjects (n=12) are needed *per group* in order to have an 80% chance of detecting a change in visceral fat volume of at least 17.9 percent, and (b) 15 subjects (n=15) are needed *per group* in order to have an 80% chance of detecting a change in insulin sensitivity of at least 17.6 percent. Therefore, our sample size for this study will be 15.

**Study drugs:** The TZD that will be used is *pioglitazone hydrochloride*. Subjects in groups 3 and 4 will begin pioglitazone 15 mg orally every day for 8 weeks total. During weeks 9-12, subjects who have tolerated 15 mg pioglitazone daily will be increased to 30 mg/day and will remain at this dose for the duration of the study. However, the pioglitazone dose may be decreased or, in rare circumstances, increased if side effects such as peripheral edema or diabetes develop (please see *Pages 13 and 14* for TZD dose adjustments). Pioglitazone has been prospectively shown to reduce visceral fat content and improve insulin sensitivity in insulin resistant people. It is begun 4 weeks prior to rhGH in order to allow sufficient time for its insulin sensitizing effect to occur. RhGH-treated subjects will begin self-injecting rhGH 8 mcg/kg SQ every day at week 5 and will continue to do so for the duration of the study, unless side effects develop (please see *Pages 13 and 14* for rhGH dose adjustments). The total rhGH treatment period will be 9 months. Previous studies have indicated that this dosage and duration of treatment are generally well tolerated and effective in significantly reducing visceral fat.

**Diet, exercise and activity:** Subjects will adhere to their usual daily dietary consumption and exercise routine for the duration of the study. They will be asked to report any significant changes in dietary intake or physical activity.

**Physical exam:** A complete physical exam will be performed at baseline (week ­- 4 to 0) and again at weeks 4, 8, 12, 16, 20, 24, 32, 40 and 43. In addition, supine systolic and diastolic blood pressure will be measured in mmHg using a manual sphygmomanometer.

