Visceral fat loss reduces postprandial glucose levels in IGT patients (13-19). Fujioka et. al showed that weight loss - and visceral fat reduction in particular - results in a significant reduction in postprandial glucose levels in viscerally obese women with IGT (20). Eriksson et. al also prospectively showed that IGT subjects achieved lower postprandial glucose levels after weight loss, and that this reduced the overall risk of developing type 2 diabetes (21). In addition, recently published data from the Diabetes Prevention Program (DPP) study indicate that a 5-7 % weight loss in IGT subjects reduces the risk of developing type 2 diabetes by 58% (22).

***GH, visceral fat reduction and enhanced insulin sensitivity:*** Growth hormone (GH), a glycopeptide hormone produced in the anterior pituitary, helps to maintain normal body composition and reduce visceral fat in adults (23). It also appears to have various effects on glucose, lipid and bone metabolism.

Viscerally obese adults have below normal integrated GH concentrations as measured by an ultrasensitive chemiluminescence assay (24). The association between visceral obesity and an apparent “underproduction” of GH has recently prompted several investigators to study the effects of rhGH on body composition and metabolism in viscerally obese adults. In a recent study, Johannsson et. al investigated the effects of rhGH in insulin resistant, viscerally obese men with normal glucose tolerance (25). As expected, subjects receiving rhGH lost a substantial amount of visceral fat – almost 18%. In addition, while overall glucose levels did not change during the study, an interesting paradoxical effect on short-term versus long-term insulin sensitivity occurred in rhGH-treated subjects. RhGH-treated subjects developed a transient *decrease* in insulin sensitivity as expected during the first 6 weeks of therapy. However, after 9 months of rhGH treatment, the glucose disposal rate (GDR), a measure of tissue insulin sensitivity*, increased* by 1.2 +/- 0.7 mg/kg per minute compared to baseline (*P* < 0.05), indicating that insulin sensitivity increases – rather than decreases - with long-term rhGH administration.

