TZDs versus diet plus exercise: An alternative approach that might obviate the need for insulin sensitizer therapy is diet and exercise. However, this approach will not be used in this study for two reasons. First, many

viscerally obese, IGT adults have already tried diet and exercise and failed. Secondly, previous studies have shown that diet and exercise cannot overcome the transient insulin resistance and hyperinsulinemia associated with rhGH (44,45).

E. **METHODS OF DATA ANALYSIS**

   Data will be analyzed using StatView software for Microsoft Windows (SAS Institute Inc., Cary, NC). All data will be expressed as the mean +/- SE. A Student’s *t* test will be used to compare baseline values of the subject groups. For measurements pertaining to visceral fat, insulin sensitivity and glucose metabolism, ANOVAs for repeated measures will be used to analyze differences between data obtained at all time points. Area under the curve (AUC) for glucose data will be determined using the trapezoid method. In addition, results will be considered significant at *P* < 0.05.

F. **SIGNIFICANCE**

A. **Prevention of type 2 diabetes** **in viscerally obese adults with IGT**

The growing health care burden of type 2 diabetes mellitus in the U.S. demands that newer, more effective diabetes prevention strategies be implemented. One way to achieve diabetes prevention is to target adults who are at greatest risk for developing diabetes, such as viscerally obese adults with IGT.

Recent studies like the Diabetes Prevention Program (DPP) Trial indicate that, in individuals with IGT, interventions that result in visceral fat reduction also significantly reduce the risk of developing overt diabetes. Unfortunately, in non-experimental settings, many obese individuals have had little success in achieving visceral fat reduction with current weight loss modalities such as diet, exercise or anorexogenic drugs. This lack of success is often related to noncompliance and recidivism with diet and exercise and with limited overall benefit, intolerable side effects and/or addictive potential with anorexogenic medications. Furthermore, the potent weight-reducing effects of bariatric surgery are often eclipsed by severe gastrointestinal complications postoperatively and, in rare circumstances, an increase in mortality.

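### The 12 and 15 per group cannot be reproduced from the printed inputs under any single reading, so the 80% power for insulin sensitivity is unsupported

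*Protocol*

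**What the plan says.** Protocol section D, Experimental Design, takes its inputs from one cited study, in which rhGH was used to "achieve a 17.9 +/- 3.5 percent change in visceral fat volume and an increase in insulin sensitivity of 1.2 +/- 0.6 mg/dl", the latter unit continuing with hr. It says that this information was used to power two primary endpoints:

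- 12 per group for an "80% chance of detecting a change in visceral fat volume of at least 17.9 percent";
- 15 per group for an "80% chance of detecting a change in insulin sensitivity of at least 17.6 percent".

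The larger figure becomes the group size, giving 60 subjects in four groups.

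Section C, Background (the part on GH and insulin sensitivity), reports the same study's gain in glucose disposal rate as an increase "by 1.2 +/- 0.7 mg/kg per minute compared to baseline", with P < 0.05.

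Under Study Endpoints, the Insulin Sensitivity Test yields a steady-state plasma glucose (SSPG) in mg/dl, and that value describes each subject's insulin sensitivity. Section E fixes the significance level: "results will be considered significant at *P* < 0.05".

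**The concern.** Insulin sensitivity is one of two primary endpoints and alone sets the trial size. The calculation behind it has four defects that can be seen in the text:

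1. The same cited result appears with two spreads (0.6 and 0.7) and two units (mg/dl hr and mg/kg per minute).
2. The +/- terms are not labelled SD or SE, and the size of the cited study is not given.
3. The 17.6% target is not tied to the quoted change of 1.2 by any baseline value.
4. The input is a glucose disposal rate, while the trial's measure is SSPG. No SSPG effect or SD is given.

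If the 80% does not follow from the inputs, a null result on insulin sensitivity could be read as adequately powered evidence of no effect when nobody can say what the power was.

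**Working it through.** **Inputs.** Fat: 17.9 +/- 3.5. Sensitivity: 1.2 +/- 0.6 (Experimental Design) or +/- 0.7 (Background). Power 80%, alpha 0.05, 15 per group. Assumed because not stated: a two-sided, two-sample t test between two groups, and a sensitivity target of 1.2.

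**What the stated figures require.** With d = difference/SD, noncentral-t power of 80% needs:

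- n = 12: d = 1.197, so SD = 17.9/1.197 = 15.0 points for fat.
- n = 15: d = 1.060, so SD = 1.2/1.060 = 1.13 for sensitivity.

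Neither SD is printed.

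**Reading 1: the +/- terms are SDs.**

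| Endpoint | d | n per group for 80% |
|---|---|---|
| Fat | 17.9/3.5 = 5.11 | 3 |
| Sensitivity, 0.6 | 1.2/0.6 = 2.00 | 6 |
| Sensitivity, 0.7 | 1.2/0.7 = 1.71 | 7 |

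Power for sensitivity at 15 per group exceeds 99% with either spread. Neither 12 nor 15 appears.

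**Reading 2: the +/- terms are SEs.** Then SD = SE x √n0, where n0 is the cited group's size (not in the protocol).

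- For fat to need 12: n0 = (15.0/3.5)² ≈ 18.
- For sensitivity to need 15: n0 = (1.13/0.6)² ≈ 3.6, or (1.13/0.7)² ≈ 2.6.

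No one n0 gives both. Holding the value that makes 12 right (n0 = 18.26 before rounding):

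| Spread | SD = SE x √18.26 | d | n per group for 80% | Power at 15 |
|---|---|---|---|---|
| 0.6 | 2.56 | 0.468 | 73 | 24% |
| 0.7 | 2.99 | 0.401 | 99 | 19% |

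For an assumed n0 of 10 to 30, power at 15 runs from 39% down to 16% with 0.6 and from 30% down to 13% with 0.7. The required n runs from 41 to 162 per group.

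**Other tests tried.**

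- Within-group change (one-sample t): 12 for fat implies n0 ≈ 33. Sensitivity then needs 67 or 91, and power at 15 is 24% or 19%.
- 2x2 interaction, SD reading, two-sided alpha 0.0083: sensitivity needs 13 or 17, but fat needs only 2.
- One-sided tests, other alphas and 90% or 95% power did not return both figures either.

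**Ratio check (conditional).** If both +/- terms are of one type, come from one group size, and the targets are the quoted effects, then on the normal approximation n is proportional to (spread/effect)². The sensitivity figure should be (5.11/2.00)² = 6.5 times, or (5.11/1.71)² = 8.9 times, the fat figure. The protocol has 15/12 = 1.25.

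**The 17.6% target.** It equals 1.2 only at a baseline of 1.2/0.176 = 6.8, which is stated nowhere.

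**A mixed reading.** If 0.6 or 0.7 is an SD, 15 per group detects 1.060 x 0.6 = 0.64 or 1.060 x 0.7 = 0.74. Setting that equal to 17.6% gives a baseline of 0.64/0.176 = 3.6 or 0.74/0.176 = 4.2. With an SE reading for fat, 12 and 15 could then both arise.

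**The case against.** The strongest reply is that irreproducible is not the same as wrong. The mixed reading above yields both figures, and the protocol never says that 17.6% means 1.2. A reader might infer that 12 and 15 cannot both be right. That inference needs both spreads to be of one type and from one group size, and 17.6% to equal 1.2. None of this is stated, so it is not supported. What the mixed reading does not do is rescue the calculation: it treats the two endpoints differently and uses a baseline that appears nowhere.

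A reader might also infer that true power is near 20%. That is only the SE branch, and its source n of about 18 is back-solved from the 12 that is itself in doubt. The SD branch gives over 99%.

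Nor does the P < 0.05 reported in the Background favour the SE reading. As an SE, 1.2/0.7 = 1.71 gives a two-sided paired-t P of about 0.12 with 10 subjects and 0.10 with 30, which misses 0.05. As an SD, P is below 0.001 from 10 subjects up, which satisfies it. The test used in the cited study is not shown, so this does not settle the matter. Section E's statement that data will be given as mean +/- SE concerns this trial's own data.

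The factorial design would also allow a 30 versus 30 comparison, but the protocol states its power per group. On the SE branch with 18 source subjects, that comparison still has only about 45% or 35% power (normal approximation).

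Two minor points stand. The gap in the printed unit may be a symbol lost in conversion, though mg/dl against mg/kg is not. The Abstract names a clamp, which might match the input's scale, but the detailed test description specifies SSPG.

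**Conclusion.** The concern holds in this form: 12 and 15 per group at 80% power cannot be reproduced from the printed inputs under any single reading, and the 80% for the endpoint that sets the trial size is therefore unsupported. The conflict of 0.6 with 0.7, and of the two units, is an error on the face of the protocol and needs no assumption.

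The size of the power problem is undetermined. Taking 1.2 as the target and a two-sided two-sample t test, power at 15 per group is above 99% if the +/- terms are SDs. It is 24% or 19% if they are SEs scaled to the stated 12, and 13% to 39% if they are SEs from an assumed 10 to 30 subjects. The documents do not choose between these, so they establish neither an underpowered trial nor an adequately powered one. They also give no reason to demote insulin sensitivity as a primary endpoint.

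**What to change.** Rewrite the sample-size paragraph in Experimental Design:

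- Check the insulin-sensitivity result against the cited study, and use one spread and one unit there and in the Background. Correct the citation number too: this paragraph gives 24, the Background gives 25.
- State whether each +/- is an SD or an SE, and the source group size.
- Recompute both figures from that one source, showing the SD actually used, the baseline behind 17.6%, the comparison and the test.
- Give the insulin-sensitivity effect and SD on the SSPG scale that the trial will measure.
- Keep 60 subjects. State the power that 15 per group gives for insulin sensitivity, or the difference detectable at 80% power (1.06 SD for a two-sided two-sample t test), in SSPG units.

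The cost is one rewritten paragraph and its matching Background figure. No subjects are added. The downside is that the stated power may turn out less favourable than 80%.

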#### STUDY ENDPOINTS

**Oral glucose tolerance test:** As per the technique described under screening, a 75 gram OGTT will be repeated at week 43, approximately 3 weeks after discontinuation of all study medications (washout period). In addition, the glucose area under the curve, or AUC, will be measured using the trapezoid method. Based on previously published data, we expect that rhGH administration will cause at least a 10% reduction in both postprandial glucose (2 hours post OGTT) and glucose area-under-the-curve compared to baseline values.

**CT of the abdomen:** A non-contrast CT of the abdomen to quantify visceral adiposity will be obtained at the baseline visit and again at week 40. This imaging technique is among the most reliable for measuring visceral fat (32). Scans will be

obtained at 5 levels: spleen/liver, L3-4 lumbar disc, L4-5 lumbar disc, lower edge of pubic symphysis, and upper thigh (with reference to edge of lower symphysis). The area of the visceral and subcutaneous abdominal fat compartments at the

5 levels will be measured and recorded in centimeters squared. Abdominal visceral volume will then be calculated (in liters) using the visceral tissue areas of the 5 scans and the measured distances between them. The same CT scanner will be used at the start and completion of the study, and the same radiologist at VA Palo Alto will analyze all scans.

**Insulin Sensitivity Test (IST):** Endogenous insulin sensitivity will be measured using a 3-hr insulin sensitivity test (33,34). This test will be performed at baseline and again at week 43 (which follows a 3-week washout period for study medications). An intravenous catheter will be placed into each antecubital vein. One catheter will be used for blood draws for glucose measurements and the catheter in the contralateral arm will be used for infusion of octreotide, insulin and 20% dextrose. The 3 infused substances will be administered simultaneously. Octreotide acetate will be used to suppress endogenous secretion of insulin and will be infused at 0.27 µg/m2 per minute. Insulin will be infused at 32 mU/m2·min and glucose will be infused at 267 mg/m2 per minute. Serum glucose will be measured every 30 minutes for the first 150 minutes and then every 10 minutes during the last half hour of the test. The last 4 serum glucose measurements will averaged and recorded in mg/dl and will constitute the subject’s steady state plasma glucose (or SSPG). The SSPG provides a direct measure of insulin-mediated glucose uptake and will be used to describe each subject’s insulin sensitivity (33,34).

**Anthropometrics:** BMI, waist circumference and WHR will be measured at baseline and at weeks 8, 16, 32 and 40.

**IGF-1 levels:** Serum insulin like growth factor 1, or IGF 1, is a marker of GH status in the body. IGF 1 levels will be drawn at baseline and again at weeks 8, 16 and 32 and will be used along with clinical symptoms to assess rhGH dose adequacy. IGF 1 values greater than 2 standard deviations above the adult reference mean will result in a 50% rhGH dose reduction.

**Liver function tests, fasting glucose, hemoglobin (Hgb) A1C:** LFTs will be obtained at baseline and again at weeks 8, 16, 24, 32 and 40. Fasting glucose levels will be measured at baseline and at weeks 4, 8, 12, 16, 20, 24, 32 and 40. A HgbA1C will be used to measure each subject’s long-term glucose control and will be obtained at baseline and at weeks 8, 16 and 40.

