**SUPPORTING INFORMATION: Trial Protocol**

# Effects of rhGH and Pioglitazone in Viscerally Obese Adults with IGT

A. **ABSTRACT**

People with impaired glucose tolerance (IGT) who lose visceral fat also tend to lower their risk of developing diabetes. This benefit occurs because visceral fat reduction improves insulin sensitivity and reduces postprandial glucose levels. Thiazolidinediones (TZDs) and growth hormone (rhGH) taken independently foran *extended period of time* can reduce visceral fat and improve endogenous insulin sensitivity. However, in the *short-term* (ie: first 6 weeks of treatment) rhGH may increase insulin resistance. In contrast, a TZD added to rhGH prevents short-term rhGH-induced insulin resistance in experimental animals, suggesting a possible therapeutic benefit with this drug combination in humans. In addition, like rhGH, TZDs mediate some of their insulin sensitizing effects by reducing visceral fat depots. It is therefore possible that the addition of a TZD with standard growth hormone therapy will optimize the short-term and long-term improvements in body composition, insulin sensitivity and glucose metabolism in humans.

The specific aims of this study are as follows: (1) to assess the effects of TZDs with and withoutrhGH on visceral fat content, insulin sensitivity and postprandial glucose levels in viscerally obese subjects with IGT; *and* (2)to compare the effects of TZDs *plus* rhGH with rhGH alone on short-term glucose metabolism. Sixty adult men and women between the ages of 40 and 75 will be recruited to participate and will receive a TZD and rhGH in a double-blind manner. During weeks 0-4, a “run-in” period, subjects will receive a TZD or oral placebo. During weeks 5-40, a TZD or oral placebo will be co-administered with rhGH or a subcutaneous placebo in a 2 X 2 study design. Short-term glucose metabolism will be monitored using fasting glucose levels. Changes in visceral fat content will be quantified using abdominal CT scanning and anthropometric measurements. At baseline and after 9 months of combination drug or placebo treatment, serum postprandial glucose levels will be measured using a standard oral glucose tolerance test, and endogenous insulin sensitivity will be measured using a hyperinsulinemic euglycemic clamp.

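### Insulin sensitivity, the primary endpoint that sets 15 per group, is a clamp in the Abstract but a post-washout SSPG test in Study Endpoints, and its 80% power rests on glucose disposal rate.

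*Protocol*

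**What the plan says.** Five places in the protocol bear on this endpoint.

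- **Abstract.** "endogenous insulin sensitivity will be measured using a hyperinsulinemic euglycemic clamp". The same sentence sets the timing: "At baseline and after 9 months of combination drug or placebo treatment, serum postprandial glucose levels will be measured". No washout is mentioned.
- **Study Endpoints, Insulin Sensitivity Test.** Octreotide, insulin and glucose are infused at fixed rates, and the last four glucose values are averaged into the SSPG, in mg/dl. On timing: "This test will be performed at baseline and again at week 43 (which follows a 3-week washout period for study medications". On meaning: "The SSPG provides a direct measure of insulin-mediated glucose uptake". The oral glucose tolerance test (OGTT) is also repeated at week 43, and that paragraph makes clear that all study drugs have by then been stopped for about 3 weeks.
- **Study Endpoints, CT of the abdomen.** Visceral fat scans "will be obtained at the baseline visit and again at week 40", the end of treatment.
- **Experimental Design.** The sizing starts from a published rhGH trial that reported "an increase in insulin sensitivity of 1.2 +/- 0.6" (printed unit mg/dl hr). It concludes that 15 per group give an "80% chance of detecting a change in insulin sensitivity of at least 17.6 percent". Visceral fat needs only 12 per group, so insulin sensitivity sets the sample size.
- **Background, GH section.** The same published trial and the same 1.2 appear here as a change in glucose disposal rate, 1.2 +/- 0.7 mg/kg per minute, after 9 months of rhGH.

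**The concern.** A clamp yields a glucose disposal rate, and a higher value means more sensitivity. A fixed-rate infusion test yields a glucose concentration, and a higher value means less sensitivity. The two differ in unit, direction and scale. A percentage change and its SD on one therefore cannot be carried to the other without a conversion, and the protocol offers none.

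Drug state differs too. The Background explains the source trial's gain as fat-loss benefit outweighing a direct rhGH antagonism, which reads as a result obtained with rhGH still acting. The endpoint here is measured with both drugs withdrawn.

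Two things are at stake. First, the power that justifies the sample size belongs to a measure the trial does not collect. Second, two of the three outcomes in Hypothesis 1 (insulin sensitivity and postprandial glucose) describe the state 3 weeks after withdrawal, while the third (visceral fat) describes the end of treatment. Specific Aim 1 then relates changes observed in two different drug states, and the protocol gives no rationale.

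**Working it through.** **Step 1: the definitions side by side.**

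| | Abstract | Source of the power input (Background) | Study Endpoints |
|---|---|---|---|
| Method | Euglycemic clamp | Not named; result is glucose disposal rate | Octreotide/insulin/glucose infusion |
| Score | Not stated | mg/kg per minute, higher = more sensitive | SSPG, mg/dl, lower = more sensitive |
| Time | After 9 months of treatment | After 9 months of rhGH | Week 43 |
| Drug state | Not stated | Apparently on rhGH (inferred) | Off all study drugs for 3 weeks |

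**Step 2: try to reproduce 15 per group.** Inputs: effect 1.2, spread 0.6 (Experimental Design) or 0.7 (Background), 80% power, and alpha from Methods of Data Analysis ("results will be considered significant at *P* < 0.05"), taken as two-sided. Sidedness, and whether the spread is an SD or an SE, are not stated.

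Normal approximation: n = 2(1.96 + 0.84)² / d².

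- Spread 0.6 as an SD: d = 1.2/0.6 = 2.0; n = 15.7/4 = 3.9, so 4 per group (6 with the two-sample t).
- Spread 0.7 as an SD: d = 1.2/0.7 = 1.71; 6 per group (7 with the t).
- Spread 0.6 as an SE: SD = 0.6√m, where m is the source group size, not given in the protocol. For m = 4, 10 and 15 the t-based n is 17, 41 and 60.

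The stated 15 does not follow from the printed inputs without a further number.

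**Step 3: what 15 per group implies.** With the two-sample t (28 degrees of freedom, critical value 2.048, noncentrality d√(15/2)), 80% power needs d = 1.06. That means an SD of 1.2/1.06 = 1.13 on the disposal-rate scale, or 17.6/1.06 = 16.6 points on the percentage scale. Neither SD is printed. If 1.2 is meant to equal 17.6%, the baseline would be 1.2/0.176 = 6.8, also not printed.

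**Step 4: sensitivity if the stated 80% is accepted.** Take d = 1.06 as given and let the week-43 effect be an assumed fraction of plan.

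| Week-43 effect, % of plan | d | Power at 15 per group | n per group for 80% |
|---|---|---|---|
| 125 | 1.325 | 94% | under 15 |
| 100 | 1.06 | 80% | 15 |
| 90 | 0.954 | 71% | 19 |
| 75 | 0.795 | 56% | 26 |
| 50 | 0.53 | 29% | 57 |

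**Step 5: sensitivity if 17.6% were the SSPG target.** The SD of percentage change in SSPG is assumed; d = 17.6/SD.

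| Assumed SD, points | d | Power at 15 per group | n per group for 80% |
|---|---|---|---|
| 15 | 1.17 | 87% | 13 |
| 20 | 0.88 | 64% | 22 |
| 25 | 0.70 | 46% | 33 |
| 30 | 0.59 | 34% | 47 |

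Both tables are ranges over assumptions. Neither estimates the trial's power.

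**The case against.** The strongest reply is that the washout is deliberate and openly stated. Week 43 does fall after 9 months of treatment, so the Abstract is incomplete on timing and does not contradict the endpoint section. Hypothesis 1 does not require testing on drug. Because the proposed mechanism is fat loss, testing off drug would reduce acute drug effects on the link between fat and sensitivity. The randomised comparison at week 43 remains valid. All of this stands, although the protocol itself offers no such rationale.

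It is also fair that SSPG and disposal rate are related measures of insulin-mediated glucose uptake, and that on-drug testing in the source trial is only an inference from the Background. Experimental Design does not name disposal rate, and its printed unit fits neither measure. The link rests on the named trial and the matching 1.2. The origin of the 17.6% is not given.

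A reader might infer that the washout costs power. The protocol does not support that. Stopping treatment removes the direct rhGH antagonism as well as the direct pioglitazone effect, so the week-43 effect could be smaller or larger than planned. Nor do the lower figures in the Step 4 table follow from the protocol's printed spread. Reading 0.6 as an SD gives d = 2.0, and power at 15 per group would still be about 98% at 75% of the effect and 75% at half of it.

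None of this answers the clamp/SSPG mismatch or the missing SSPG inputs.

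**Conclusion.** The point holds in this form. One primary endpoint carries two different measurement methods, and the power figure that sets the sample size is taken from a third description, glucose disposal rate, without conversion. The stated 80% is therefore unsupported for SSPG at week 43. The protocol does not show that the trial is underpowered, that the post-washout design is wrong, or that its results would be invalid.

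The true power cannot be computed. Accepting 80% at 15 per group, it runs from about 94% to 29% as the week-43 effect goes from 125% to 50% of plan. With 17.6% as the SSPG target, it runs from about 87% to 34% for an SD of 15 to 30 points. Both ranges assume a two-sample t test, two-sided 5%, 15 evaluable subjects per group, and effects or SDs that the protocol does not supply.

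This should be corrected because it concerns the definition and sizing basis of a primary endpoint.

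**What to change.** Reconcile the Abstract, Hypothesis 1 with Specific Aim 1, Experimental Design and Study Endpoints to one method, one time point and one drug state. Which state to study is the sponsor's choice.

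If the week-43 test stays:

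- name SSPG as the endpoint throughout, with a fall counted as improvement;
- restate the power in SSPG units with a stated SD, target difference and source, or withdraw the 80% claim for this endpoint;
- limit the insulin-sensitivity and OGTT conclusions to the state 3 weeks after stopping treatment;
- say in Specific Aim 1 that an end-of-treatment fat change is being related to off-drug sensitivity and glucose, and give the reason.

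If sensitivity during treatment is the question, the endpoint section's timing must be brought into line with that.

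Keeping week 43 costs wording and one recalculation, with no new procedure. The price is a narrower claim and possibly a less favourable stated power.
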